## Abstract

**Aim(s):**

The aim of this study is to assess the impact of a stress management intervention on the prevention of Post-Intensive Care Syndrome-Family (PICS-F).

**Design:**

A single-center, prospective, parallel-design, randomized controlled trial (RCT) study.

**Methods:**

This study will recruit 56 family members of ICU patients from a hospital in China. Participants will be randomly assigned to either the experimental group or the control group. The control group will receive standard care, and the experimental group will receive standard care plus a stress management intervention. The primary outcome is a composite score of psychological distress (integrating perceived stress, anxiety, and depression) measured immediately post-intervention. Secondary outcomes include the longitudinal trajectories of individual psychological symptoms (stress, anxiety, depression), symptoms of post-traumatic stress, and sleep quality across multiple follow-ups up to 90 days. Data analysis will be performed utilizing IBM SPSS version 27.0 software.

**Discussion:**

This study protocol describes a RCT aimed at evaluating the effectiveness of the stress management intervention measures in preventing the occurrence of the PICS-F among family members of patients in the intensive care unit.

**Clinical trial registration:**

https://www.chictr.org.cn/bin/project/edit?pid=272710, identifier ChiCTR2500102953.

## Introduction

1

In the Intensive Care Unit (ICU), the primary objective of the medical staff is to preserve patients’ lives and minimize the incidence of complications, given the critical nature of their conditions (Laux et al., 2023). For the families of patients, medical staff are usually limited to informing the patients of the current status of the disease, treatment measures and progress, and pay less attention to the psychological and emotional support of the families (Gu et al., 2023; Li and Huang, 2020; Mi et al., 2021; Ran, et al., 2023). ICU patients are often in critical condition, with many in a comatose state. The physical and mental health of family members, who serve as primary caregivers and clinical decision-makers, significantly influence the patients’ eventual clinical recovery outcomes (Lin et al., 2020). The high cost of treatment, sudden hospitalization of critically ill relatives, restricted ICU visitation hours, lack of familiarity with the ICU environment, fear of uncertain disease prognosis, and the need to make clinical decisions on behalf of patients—all these factors impose a heavy burden on family members, leading to physical, psychological, and social dysfunction, a condition referred to as Post-Intensive Care Syndrome-Family (PICS-F) (Davidson et al., 2012; Davidson and Harvey, 2016). Among these, psychological disorders encompass stress, anxiety, depression, post-traumatic stress disorder (PTSD), and complex grief, with anxiety and depression being the most prevalent (Hayes et al., 2024).

Research indicates that the prevalence of PICS-F ranges from 6 to 69% within 6 months following the discharge of patients from the ICU (Petrinec and Martin, 2018). 58.1% of family members are likely to experience moderate to severe sleep disturbances, while 57.6% may suffer from significant fatigue (Dayet et al., 2013). In a survey conducted among 350 family members of ICU patients in Turkey, 81.4% of respondents reported experiencing anxiety, while 94.2% reported symptoms of depression (Çelik et al., 2016). When PICS-F occurs, it can persist for 5–15 years, severely impacting patients’ and families’ quality of life, escalating medical resource needs, and burdening society (Gu et al., 2023; Voiriot et al., 2022). Research on the elevated incidence of PICS-F suggests that implementing appropriate intervention strategies is essential to prevent its onset and progression (Elliott et al., 2014). However, in recent years, the majority of studies pertinent to the field of critical care have predominantly concentrated on patients, often neglecting the experiences and needs of their families. In fact, regardless of whether ICU patients survive or not, their family members may develop post-ICU syndrome, and the psychological disorders of family members are more severe and last longer than those of ICU survivors (Fumis et al., 2015). This phenomenon may be attributed to the challenges faced by patients discharged from the ICU, which include physical and psychological impairments, diminished quality of life, and difficulties in reintegrating into society (Ho and Li, 2023). Approximately 25% of these patients require ongoing informal care services within 6 months to 1 year post-discharge, with around 80% of this care being provided by family members (Griffiths et al., 2013). As the main caregivers of discharged patients from the ICU, family members often have to undertake multiple responsibilities, including: being responsible for the patients’ diet, medication, physical care and medical arrangements, as well as independently undertaking all household chores, taking care of children, social life and other responsibilities that should have been borne by the patients (Choi et al., 2018; Czerwonka et al., 2015; van Beusekom et al., 2016). Some family members may reduce their working hours or leave their jobs to provide care for patients, resulting in a decline in their economic status and imposing a significant financial burden on the family (Zeng, 2023). Current evidence suggests that the stress experienced by family members during a patient’s hospitalization in the ICU elevates the risk of developing PICS-F (Davidson et al., 2017). However, there remains a paucity of effective intervention strategies to mitigate this stress.

In light of this, we established a multidisciplinary team to develop a psychological intervention termed Sensation Awareness Focused Training (SAF-T). Grounded in psychophysiological theory, SAF-T integrates Eye Movement (EM) techniques—derived from Eye Movement Desensitization and Reprocessing (EMDR) therapy—with breathing and relaxation exercises. By engaging working memory through dual-task loading, enhancing interhemispheric communication, performing smooth-pursuit eye movements, and practicing slow, deep breathing, this approach reduces sympathetic nervous system arousal. This process facilitates a calming response, interrupts negative thoughts, emotions, and behaviors, alleviates stress, and helps prevent the onset of anxiety and depression (Lee and Cuijpers, 2013). Eye movements not only activate large-scale default mode network activity while attenuating frontoparietal control network activity—thereby releasing functions such as self-reflection, memory retrieval, and associative learning while temporarily suppressing physiological arousal and the high cognitive load induced by traumatic memories—but may also activate two emotion regulation pathways: the cerebellar-thalamic-prefrontal pathway and the cerebellar-hypothalamic-limbic pathway (Zou et al., 2025). This dual activation minimizes defensive emotional responses during SAF-T. Voogd et al. found that eye movements can promote interhemispheric and intrahemispheric interactions, thereby facilitating adaptive memory integration (Voogd and Linda, 2017). Extensive literature also indicates that repeated eye movements may activate the parasympathetic nervous system and elicit a bodily relaxation response (Barrowcliff et al., 2003; Elofsson et al., 2008; Stickgold, 2002). Finally, the physiological effects of deep breathing in SAF-T, which activates the parasympathetic nervous system, contribute to stress and anxiety reduction (Jerath et al., 2006).

This study will employ a randomized controlled trial (RCT) design to examine the efficacy of SAT-F, a stress management intervention, in preventing PICS-F (stress, anxiety, depression, PTSD, and sleep quality) among family members of patients in the intensive care unit during their hospitalization.

### Study aims and hypotheses

1.1

The primary objective of this RCT is to evaluate the immediate efficacy of the SAF-T intervention in alleviating psychological distress (a composite of stress, anxiety, and depressive symptoms) among family members of ICU patients, as measured on Day 3 post-enrollment (immediately after intervention completion). Secondary objectives include: (1) To assess the longitudinal trajectories of stress, anxiety, and depressive symptoms in family members receiving the SAF-T intervention, examining its sustained effects at Day 3 post-enrollment (post-intervention), upon patient transfer from the ICU, and at the Day 30 and Day 90 follow-ups. (2) To explore the potential of the SAF-T intervention for preventing PTSD symptoms, measured at Day 3 post-enrollment (post-intervention), upon patient transfer from the ICU, and at the Day 30 and Day 90 follow-ups. (3) To explore the effect of the SAF-T intervention on sleep quality, measured at Day 3 post-enrollment (post-intervention), upon patient transfer from the ICU, and at the Day 30 and Day 30 follow-ups.

Based on the objectives above, the following hypotheses are proposed: (1) Primary Hypothesis: Compared to family members receiving usual care (control group), those receiving the SAF-T intervention will demonstrate a significantly lower composite score of psychological distress after completing the 3-day intervention period (Day 3 post-enrollment). (2) Secondary Hypotheses: (1) Compared to the control group, the intervention group will show greater reductions or faster improvement in individual scores on the perceived stress scale (PSS-10), generalized anxiety disorder scale (GAD-7), and patient health questionnaire (PHQ-9) from baseline to each follow-up assessment. (2) Compared to the control group, the intervention group will have significantly lower impact of event scale-revised (IES-R) scores (indicating fewer PTSD symptoms). (3) Compared to the control group, the intervention group will have significantly lower sleep quality index (PSQI) scores.

## Methods and analysis

2

### Study design and setting

2.1

This research will employ a single-center, prospective, parallel-design, RCT protocol, meticulously following the CONSORT guidelines. This study will be conducted in the ICU of a tertiary-grade a general hospital located in China. The study protocol was approved by the ethics committee and registered in the Chinese Clinical Trial Registry.

#### Participants

2.1.1

This study will recruit family members of ICU inpatients who fulfill the specified inclusion and exclusion criteria as research subjects. Members of the research team will review the electronic medical records within the hospital information system to preliminarily identify eligible family members. Subsequently, face-to-face communication and assessments will be conducted with those family members who meet the research criteria, ultimately leading to the selection of individuals who satisfy the study’s conditions. All participants will provide informed consent prior to their involvement in the study.

The inclusion criteria for this study are as follows: patients must be admitted to the ICU for a minimum duration of 24 h; family members, defined as parents, children, spouses, or siblings, must be aged 18 years or older; each patient will be represented by a single primary caregiver responsible for medical decision-making; family members must have no prior history of mental illness or severe organic diseases; and family members must provide informed consent and voluntarily agree to participate in the study. The exclusion criteria include: patients who are unidentified, unaccompanied, and lack financial support, which renders family contact unfeasible; and family members who possess severe hearing or speech impairments that hinder their ability to participate in the study. The withdrawal criteria for this study are as follows: incomplete assessment of baseline data and primary indicator evaluation data; and noncompliance with the research protocol as stipulated. When a participant withdraws from the study, researchers should make every effort to contact the individual through various methods, including phone calls and online communication, to inquire about and document the reasons for their withdrawal. All randomized participants will be analyzed according to the intention-to-treat (ITT) principle upon trial completion, irrespective of their adherence to or completion of the intervention protocol.

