### Statistical analysis

2.6

In this study, EpiData3.1 software will be utilized for data entry, while IBM SPSS Statistics version 27.0 will be employed for data analysis.

All statistical tests were two-sided with *α* = 0.05, and *p* < 0.05 indicated significance. Categorical variables, including family member demographics, will be presented as counts and percentages and compared between groups using the *chi-square* test or *Fisher’s* exact test, as appropriate. Continuous variables will be assessed for normality using the *Shapiro–Wilk* test. Normally distributed data will be summarized as mean ± standard deviation, while non-normally distributed data will be summarized as median and interquartile range. For baseline comparisons of continuous variables, independent samples *t*-tests or *Mann–Whitney U* tests will be applied accordingly. For the intention-to-treat (ITT) analysis, missing data from participants who withdraw during the study will be handled using multiple imputation (MI). Specifically, the multiple imputation module in SPSS version 27.0 will be employed to create five complete datasets using the fully conditional specification method, with group allocation, time point, baseline scores, and demographic characteristics included as predictor variables. The imputed results will then be pooled for analysis.

Primary Outcome Analysis: The primary analysis will follow the ITT principle, including all randomized participants. The efficacy of the SAF-T intervention will be assessed by comparing the psychological distress composite score at the primary endpoint (Day 3) between the intervention and control groups, adjusting for the baseline composite score. (1) Calculation of the composite score. To ensure comparability across time points, all composite scores will be standardized using the means and standard deviations calculated from the Day 3 assessments. For each participant at Day 3, the composite score will be calculated as follows: First, for each of the three scales (PSS-10, GAD-7, and PHQ-9) administered at Day 3, the mean (
${\overset{ˉ}{x}}_{k}$
) and standard deviation (
$SD_{k}$
) will be calculated across all participants, where 
k=1,2,3
 represents the three scales, respectively. Second, for each participant 
i
, the raw score on each scale (
$x_{\mathrm{ik}}$
) will be standardized to a Z-score: 
$Z_{\mathrm{ik}}=\frac{x_{\mathrm{ik}}-{\overset{-}{x}}_{k}}{SD_{k}}$

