. Finally, the three standardized scores will be summed to obtain the participant’s psychological distress composite score: 
$\text{CompositeScor}e_{i}=Z_{i,\mathrm{PSS}-10}+Z_{i,\mathrm{GAD}-7}+Z_{i,\mathrm{PHQ}-9}.$
 (2) Primary statistical model. The primary between-group comparison at Day 3 will be performed using an analysis of covariance (ANCOVA), with the Day 3 composite score as the dependent variable, experimental group as the fixed factor, and the baseline composite score as a covariate. Prior to ANCOVA, normality of residuals and homogeneity of regression slopes will be assessed. If the assumptions of ANCOVA are violated, a non-parametric alternative (e.g., Quade’s rank ANCOVA) will be applied. (3) Effect size and validation. To assess the clinical significance of the intervention effect, Cohen’s d effect size will be calculated, with *d* = 0.2 considered a small effect, *d* = 0.5 a medium effect, and *d* = 0.8 a large effect (Bartko et al., 1988). As a validation step, the theoretical standard deviation of the composite score will be computed using the variance sum theorem: 
$SD_{\text{theoretical}}=\sqrt{3+2(r_{12}+r_{13}+r_{23})}$
. where 
$r_{12}$
, 
$r_{13}$
, and 
$r_{23}$
 represent the Pearson correlation coefficients between each pair of the three scales. This theoretical value will be compared with the observed standard deviation to confirm the construct validity of the composite score. (4) Sensitivity analyses. As a sensitivity analysis, a per-protocol (PP) analysis will be conducted to evaluate the robustness of the primary ITT results. Additionally, to assess the potential impact of contamination, we will perform an analysis excluding control group participants who received protocol-prohibited psychological support during the intervention window.

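### Noncompliance is a criterion for withdrawal from the study, which conflicts with the ITT promise and, if outcome collection then ends, moves the primary estimate towards the effect in compliers

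*Protocol article*

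**What the plan says.** Protocol article, section 2.1.1 (Participants), lists two withdrawal criteria: "incomplete assessment of baseline data and primary indicator evaluation data; and noncompliance with the research protocol as stipulated". The next sentence concerns people who withdraw from the study. It says they are contacted "to inquire about and document the reasons for their withdrawal" and does not mention collecting outcomes. The paragraph ends with the opposite commitment: "All randomized participants will be analyzed according to the intention-to-treat (ITT) principle upon trial completion, irrespective of their adherence to or completion".

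Section 2.6 (Statistical analysis) repeats that commitment: "The primary analysis will follow the ITT principle, including all randomized participants". For the ITT analysis, "missing data from participants who withdraw during the study will be handled using multiple imputation (MI"), using five data sets from fully conditional specification, "with group allocation, time point, baseline scores, and demographic characteristics included as predictor variables". The longitudinal part of 2.6 again names MI for missing Day 3 outcomes and relies on missing-at-random (MAR) mixed models for later visits. As a check, "a per-protocol (PP) analysis will be conducted to evaluate the robustness of the primary ITT results".

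Two other places bear on the point. Section 2.2.2 lets participants pause or stop the intervention, which is a different event from leaving the study. Section 2.2.1 keeps controls who received prohibited psychological support in the primary comparison.

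**The concern.** An ITT estimate needs the outcomes of people who did not adhere. A rule that takes people out of the study because they did not adhere works against that, even if their names stay in the analysis set. The plan itself links withdrawal to missing data and then to imputation. The listed predictors do not distinguish a SAF-T participant who stopped from one who completed, so a withdrawn non-complier would receive a Day 3 score like that of participants who stayed.

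The effect would fall mainly on one arm, because the three sessions are required only there. It may also be related to the outcome: section 2.2.2 anticipates sessions interrupted by crying, agitation or expressions of hopelessness, and the primary outcome is psychological distress.

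The planned robustness check would not show the problem. If non-compliers have no Day 3 score, the imputed ITT analysis and the per-protocol analysis rest largely on the same observed people, so they would tend to agree. The mixed models for Day 30 and Day 90 share the MAR assumption.

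**Working it through.** **The plan's own figures.** No stated figure is disputed here. The sample size in section 2.1.2 reproduces: a two-sample t-test with d = 1.13, two-sided α = 0.05 and power 0.95 needs 22 per group, and 22 / 0.80 = 27.5, rounded up to 28.

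**The statements side by side.**

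| Question | Text | Consequence |
|---|---|---|
| Who is in the primary analysis? | All randomised (2.1.1, 2.6) | No conflict over the analysis set |
| Who leaves the study? | Non-compliers and those with incomplete assessments (2.1.1) | Conflicts with analysis irrespective of adherence |
| What happens after withdrawal? | Contact to record reasons (2.1.1) | Outcome collection is neither promised nor ruled out |
| How are missing values filled? | MI from group, time point, baseline scores, demographics (2.6) | Adherence plays no part |

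**Size, as an illustration.** The article gives no noncompliance rate. Assumptions:
- p = share of the SAF-T arm that is non-compliant, 10–30%.
- d = effect in compliers, 0.70 SD, the value that section 2.1.2 calls a clinically meaningful target.
- Non-compliers have no benefit.
- q = share of non-compliers with no Day 3 score.

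True ITT effect = (1 − p)·d.

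Imputation gives each missing non-complier the average of the observed SAF-T participants at the same baseline. The observed fraction of the arm is 1 − pq and only compliers benefit, so the estimate is d·(1 − p) / (1 − pq).

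With q = 1 (no non-complier has a score) this equals d:

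| p | True ITT effect | Estimate | Overstatement | Ratio 1/(1 − p) |
|---|---|---|---|---|
| 10% | 0.90 × 0.70 = 0.63 | 0.70 | 0.07 SD | 1.11 |
| 20% | 0.80 × 0.70 = 0.56 | 0.70 | 0.14 SD | 1.25 |
| 30% | 0.70 × 0.70 = 0.49 | 0.70 | 0.21 SD | 1.43 |

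The role of q at p = 20%:
- q = 0: 0.56 / 1 = 0.56, no bias.
- q = 0.5: 0.56 / 0.90 = 0.62.
- q = 1: 0.56 / 0.80 = 0.70.

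**Simulation check.** ANCOVA with 28 per arm, baseline correlation 0.5 and 3,000 runs per scenario. Non-compliers were either followed or removed, removal standing in for the expected result of MAR imputation from arm and baseline. For p = 10, 20 and 30%, following everyone gave 0.625, 0.562 and 0.487 SD; removal gave 0.696, 0.703 and 0.695 SD.

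If non-compliers also do 0.3 SD worse, the true ITT effect is 0.70(1 − p) − 0.3p = 0.60, 0.50 and 0.40 SD. Removal still returns about 0.70, so the overstatement is 0.10 to 0.30 SD.

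**The other criterion.** An incomplete primary assessment is itself a missing value. Imputing it is compatible with ITT under MAR and does not pull the estimate towards compliers unless the missingness goes with noncompliance. Its cost as a withdrawal criterion is that someone who misses Day 3 may also be lost at ICU discharge, Day 30 and Day 90.

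**The case against.** The strongest reply is that the article never says collection stops at withdrawal or that observed scores are discarded. Section 2.6 imputes missing data only, so a non-complier with a Day 3 score has nothing to impute. Section 2.2.2 separates stopping the intervention from leaving the study, and section 2.2.1 keeps one kind of protocol deviation in the primary comparison, which suggests that deviations are not automatically treated as missing. A condensed article may also leave the detail of follow-up after withdrawal to the full protocol.

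Most of this stands, and it rules out several stronger readings that a reader might draw:
- That the plan deliberately ends data collection for non-compliers. The text is silent on this, so the bias is conditional.
- That randomised people are excluded from the primary analysis. They are not.
- That noncompliance can arise only in the SAF-T arm. The wording is noncompliance with the research protocol, and controls can also depart from it. Mainly is as far as the text goes.
- That both criteria bias the estimate towards compliers. Only noncompliance does so directly. For the baseline part, the article does not state whether baseline collection precedes opening the envelope.
- That the overstatement is known to be 11, 25 or 43%. Those ratios rest on an assumed rate, on no benefit at all (even after one or two sessions), and on no Day 3 score from any non-complier.

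The reply does not remove the contradiction. Section 2.1.1 attaches noncompliance to leaving the study, not to stopping the intervention. It describes later contact only to record reasons and, in the same paragraph, promises analysis irrespective of adherence. That is a rule stated wrongly, not a detail left out.

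**Conclusion.** The point holds as an internal conflict with a conditional bias. Withdrawing people from the study for noncompliance cannot be squared with an ITT analysis irrespective of adherence, and the imputation model cannot repair the difference. The conflict concerns who is still measured and what the primary estimate means, not who is in the analysis set.

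To the extent that withdrawal ends outcome collection, the bias is towards the effect in compliers: between nothing (all Day 3 scores obtained) and, under the illustrative assumptions of 10–30% noncompliance without benefit, 0.07 to 0.21 SD on a complier effect of 0.70 SD. The article supplies neither the rate nor the share of non-compliers left unmeasured, so no figure can be put on this trial. The direction is clear, and the matter should be settled before more participants are followed, because a Day 3 score not taken cannot be recovered.

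**What to change.** Reconcile sections 2.1.1 and 2.6 as follows:
1. Remove noncompliance and incomplete primary assessment as criteria for withdrawal from the study.
2. Separate stopping the intervention from leaving the study. Anyone who misses sessions or an assessment stays in follow-up at Day 3, ICU discharge, Day 30 and Day 90, and observed scores are used, unless the participant withdraws consent.
3. Use noncompliance only to define the per-protocol set.
4. Require complete baseline questionnaires before the envelope is opened, so that incomplete baseline data cannot be a post-randomisation reason for withdrawal.
5. Reserve MI for outcomes that could not be obtained.

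The cost is a change of protocol wording and a few more telephone assessments that are already in the schedule (Table 3). The effect estimate may be smaller, because it will include people who did not complete the programme; that is what the ITT label promises.
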